### Power estimations for secondary outcomes based on a sample size of 2 × 190 participants

#### Major and minor complications

With a 5% acceptable risk of type I error, a proportion of major complications in the control group of 12%, a relative risk reduction of 20%, we will have 8.7% power when assessing this outcome.

#### Length of hospital stay (hours)

With a sample size of 190 women in each arm of the study, an alpha value of 5% and an average discharge of 48 h postoperatively versus 40 h, and a standard deviation of 25 h, we have a power of 84%.

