#### Operative time

With a sample size of 190 women in each arm of the study, an alpha value of 5% and an average operation time of 101 min in the 2D group, and an operation time of 90 min in the 3D group, and a standard deviation of 36 min, we have a power of 81%.

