### Trial strengths and limitations

This trial has a number of strengths. First, the randomized design makes it possible to validly assess the effects of the two surgical interventions. Second, the trial has a high degree of external validity because we assess the effects of operative procedures as they are performed in most gynecological departments and we use two recruiting centers. Third, the risk of systematic errors is reduced by central randomization stratified for prognostic factors [16, 17], blinding is used to the highest possible extent, and data is analysed according to the intention-to-treat principle. Fourth, in trials investigating operative procedures it is often difficult to distinguish whether different effects of the operative techniques or varying skills of the surgeon cause a supposed difference. In this present trial the same experienced surgeons perform both the conventional and 3D operations. This, together with the overall low risk of bias of this trial, contributes to a high degree of internal validity. Finally, we estimated a sample size adjusted for two primary outcomes using realistic anticipated intervention effects and we performed power calculations for all secondary outcomes, and we planned to adjust the thresholds for significance if we do not reach the planned sample size. This limits the risks of random error [14].

A limitation of this trial is that we will probably not be able to detect a difference in complication rate between the 2 arms of the trial. The overall low complication rate following laparoscopic hysterectomy requires a large sample size to detect a possible difference. We expect it is more likely to demonstrate a difference in postoperative pain or quality of life, two other relevant clinical outcomes that have not previously been assessed following 3D laparoscopic hysterectomy.

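### The stated powers for length of stay (84%) and operative time (81%) do not follow from their stated inputs; at two-sided 5% they are about 88% and 84–85%

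*Protocol article*

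**What the plan says.** Under the heading on power for secondary outcomes, the protocol article gives three figures for 190 women per arm.

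- **Length of hospital stay:** "an alpha value of 5% and an average discharge of 48 h postoperatively versus 40 h, and a standard deviation of 25 h", leading to "we have a power of 84" per cent.
- **Operative time:** "an alpha value of 5% and an average operation time of 101 min in the 2D group", then "an operation time of 90 min in the 3D group, and a standard deviation of 36 min", leading to "we have a power of 81" per cent.
- **Major complications:** at 5%, with 12% in the control group, "a relative risk reduction of 20%, we will have 8.7% power when assessing this outcome".

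The Statistical analyses section specifies two-sided tests and linear regression for continuous outcomes. The Randomization section gives 1:1 allocation. The type I error of 3.3% appears in the sample size section, where it is tied to there being two primary outcomes.

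**The concern.** The two sections on continuous outcomes state every input that a power calculation needs, so the printed results can be checked directly. Both come out lower than the inputs imply, by a similar amount. That is more than rounding or the choice between a normal and a t calculation can explain. Either the powers or the alpha beside them must therefore be wrong.

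What is at stake is the accuracy of two stated operating characteristics. A reader who relies on them will think the trial slightly less able to detect these differences than it is under the stated assumptions.

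**Working it through.** **Inputs, all from the article.** n = 190 per arm, 1:1, two-sided tests, comparison of means. Stay: difference 48 − 40 = 8 h, SD 25 h. Operative time: difference 101 − 90 = 11 min, SD 36 min. Stated alpha: 5%.

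**Formula.** Power ≈ Φ(δ/SE − z), with SE = SD × √(2/n) and z the two-sided critical value: 1.960 at 5%, 2.132 at 3.3%. Each result was also checked with the noncentral t distribution on 378 degrees of freedom.

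**Length of stay**
- SE = 25 × √(2/190) = 2.565 h; δ/SE = 8/2.565 = 3.119.
- At 5%: Φ(3.119 − 1.960) = Φ(1.159) = 87.7% (t: 87.5%). Stated: 84%.
- At 3.3%: Φ(3.119 − 2.132) = Φ(0.987) = 83.8% (t: 83.6%).

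**Operative time**
- SE = 36 × √(2/190) = 3.694 min; δ/SE = 11/3.694 = 2.978.
- At 5%: Φ(2.978 − 1.960) = Φ(1.018) = 84.6% (t: 84.4%). Stated: 81%.
- At 3.3%: Φ(2.978 − 2.132) = Φ(0.846) = 80.1% (t: 79.9%).

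| Outcome | Stated | Two-sided 5% | Two-sided 3.3% | Shortfall against 5% |
|---|---|---|---|---|
| Length of stay | 84% | 87.5–87.7% | 83.6–83.8% | 3.5–3.7 points |
| Operative time | 81% | 84.4–84.6% | 79.9–80.1% | 3.4–3.6 points |

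**Other routes to the printed figures.** A one-sided 5% test is further away (93.0% and 90.9%). Using 171 per arm at 5%, that is 190 less 10%, gives 84.1% and 80.7%, which round to both printed values. The article states no such loss, however, and names 190 in both sections.

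**Major complications, for comparison.** The rates are 12% and 12% × 0.8 = 9.6%, with n = 190 and alpha 5%. The difference is 0.024 and the continuity correction is 1/190 = 0.00526. The standard errors are 0.03184 (pooled) and 0.03182 (unpooled).
- Upper tail: Φ[(0.024 − 0.00526 − 1.960 × 0.03184)/0.03182] = Φ(−1.373) = 8.49%.
- Lower tail: Φ[(−0.024 − 0.00526 − 1.960 × 0.03184)/0.03182] = Φ(−2.881) = 0.20%.
- Sum: 8.69%, which is the printed 8.7%.

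Without the correction, power at 5% is 11.4% (11.7% counting both tails).

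**The primary outcomes at each alpha.** n per arm = 2 × [SD × (z + 1.282)/δ]², for 90% power.
- Pain (10 mm, SD 20 mm): 94 at 3.3%, 85 at 5%. Stated: 92 at 3.3%.
- SF-36 (4 points, SD 12): 210 at 3.3%, 190 at 5%. Stated: 190 at 3.3%.

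**The case against.** The strongest reply is that the error is harmless. It understates power, both outcomes stay at or very near 80% or above on either alpha, and the SF-36 calculation, not these outcomes, sets the trial size. All of that stands, and it limits the weight of the point. It does not make the printed figures correct.

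A reader might also infer more than the article supports:

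- **That the primary and secondary alphas were interchanged.** The SF-36 number of 190 does fit 5% rather than its stated 3.3%, and the two powers here lie near 3.3%. But the pain number of 92 is close to the answer at its own stated 3.3% (94) and not to that at 5% (85). Operative time at 3.3% rounds to 80%, not 81%, and an unstated 10% loss at 5% fits both printed powers at least as well. The cause is not established.
- **That 8.7% for complications is also wrong.** It is reproduced at its stated 5% by a continuity-corrected two-sided test. The planned analysis is logistic regression, but that section names no test for the power figure, and a corrected test is a common conservative approximation.
- **That the significance threshold for secondary outcomes is unclear.** All three secondary sections state 5%, and the Statistical analyses section links 0.033 to the number of primary outcomes. A misprinted power does not change a decision rule.
- **That the claim "we performed power calculations for all secondary outcomes" is a further error of this kind.** No power is shown for the SF-36 mental health score or for minor complications, so the word all goes beyond what is reported. That is a matter of wording in the discussion and changes no result.

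**Conclusion.** The point holds for two figures. At the stated 190 per arm, two-sided 5% and the stated means and standard deviations, power is about 88% for length of stay (stated 84%) and 84–85% for operative time (stated 81%). Both are understated by about 3.5 percentage points.

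This rests on a comparison of means between equal arms with all 190 women per arm contributing, as the article says. The closeness to 3.3% is an observation, not a demonstrated explanation. The matter is minor: the error is conservative, and it affects neither the sample size nor any planned analysis.

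**What to change.** Choose one of the following for the sections on length of stay and operative time:

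1. Keep the stated 5% and print about 88% and 84–85%. This agrees with the alpha given in all three secondary sections.
2. If 3.3% was the alpha actually used, correct the stated alpha in these two sections and print 84% and 80%.

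If an allowance for loss to follow-up was built in, state it together with the number evaluable per arm. The complications figure needs no correction. The cost is two corrected lines, with no change to design, sample size or analysis.

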#### Operative time

With a sample size of 190 women in each arm of the study, an alpha value of 5% and an average operation time of 101 min in the 2D group, and an operation time of 90 min in the 3D group, and a standard deviation of 36 min, we have a power of 81%.

### Missing data

All analyses are performed according to the intention- to-treat principle. In case of less than 5% of missing data for the randomized participants for primary and secondary outcome, a complete case analysis will be performed. In case of more than 5% missing data, multiple imputations will be used to handle missing data. We will additionally perform a sensitivity analysis using a best-worst and worst-case scenario imputation [14].

#### Ethical considerations

When conducting medical intervention studies, ethical considerations are always essential. This trial is important because it is in the interest of the patient as well as the health system to optimise surgery and minimise adverse outcomes without an unreasonable increase in medical device expenses. Gynaecological examination and operation are associated with discomfort to some extent, but patients with relevant symptoms are undergoing these procedures whether or not they are included in the trial. Furthermore, available evidence suggests that 3D technology is at least as good as the current technology. Thus, we provide the best-proven standard of operation for both groups, and it is very unlikely that we increase risks for the patients by performing 3D laparoscopy. Further all relevant information including undesirable medical events occurring during the clinical trial, presumably caused by the operation, will be reported to the Danish Hysterectomy and Hysteroscopy Database (DHHD).

We have designed the trial so that the risk of systematic errors and bias is minimised and therefore, data will be meaningful and improve future laparoscopic surgery.

## Discussion

The presented randomized trial is designed to investigate the beneficial and harmful effects of 3-dimensional versus conventional laparoscopy in patients undergoing benign laparoscopic hysterectomy. A previous retrospective study suggests that operative time for hysterectomy is significantly lower for 3D compared to conventional laparoscopy [12]. Complication rates were not statistically different, but this conclusion was limited by a small number of patients in each group. So far, no trials have examined whether 3D laparoscopy has an impact on postoperative pain or quality of life after return to daily activities.

3D laparoscopy offers a 3-dimensional stereoscopic imaging combined with preserved tactile sense as in a conventional laparoscopic set-up, and 3D laparoscopy might therefore refine and optimise surgery. However, we do not know whether 3D laparoscopy offers clinical benefit compared to conventional laparoscopic, whether the potential beneficial effects are relevant for the patient, or whether 3D laparoscopy causes unexpected adverse effects.

The price of 3D laparoscopy is higher than for 2D equipment, but lower than for robotic surgery. As medical equipment is becoming increasingly sophisticated and expensive, it is essential to determine whether 3D has relevant effects in clinical practise before it is implemented as part of the daily routine.

We hope that this trial will help place 3D laparoscopy in the range of endoscopic approaches for benign hysterectomy.

### Trial strengths and limitations

This trial has a number of strengths. First, the randomized design makes it possible to validly assess the effects of the two surgical interventions. Second, the trial has a high degree of external validity because we assess the effects of operative procedures as they are performed in most gynecological departments and we use two recruiting centers. Third, the risk of systematic errors is reduced by central randomization stratified for prognostic factors [16, 17], blinding is used to the highest possible extent, and data is analysed according to the intention-to-treat principle. Fourth, in trials investigating operative procedures it is often difficult to distinguish whether different effects of the operative techniques or varying skills of the surgeon cause a supposed difference. In this present trial the same experienced surgeons perform both the conventional and 3D operations. This, together with the overall low risk of bias of this trial, contributes to a high degree of internal validity. Finally, we estimated a sample size adjusted for two primary outcomes using realistic anticipated intervention effects and we performed power calculations for all secondary outcomes, and we planned to adjust the thresholds for significance if we do not reach the planned sample size. This limits the risks of random error [14].

A limitation of this trial is that we will probably not be able to detect a difference in complication rate between the 2 arms of the trial. The overall low complication rate following laparoscopic hysterectomy requires a large sample size to detect a possible difference. We expect it is more likely to demonstrate a difference in postoperative pain or quality of life, two other relevant clinical outcomes that have not previously been assessed following 3D laparoscopic hysterectomy.

## Abbreviations

3D: 3-dimensional
Tv. UL: Transvaginal ultrasound
UL: Ultrasound
